The high-dose group will show a greater improvement in a range of alcohol consumption parameters than the active placebo group (↓ % of heavy drinking days at 6 months posthospital discharge, ↓ drinks per day and ↑ % of days of abstinence at 4 weeks and 6 months posthospital discharge).The high-dose group will demonstrate greater reductions in depression, anxiety, and subsyndromal trauma symptoms, as well as a greater improvement in health-related quality of life compared to the active placebo group.The high-dose group will demonstrate greater increases in psychological flexibility and connectedness than the active placebo group. These increases will correlate with clinical outcomes.The high-dose group will show a greater increase in neuroplasticity compared to the active placebo group, as measured with the EEG-derived auditory long-term potentiation (LTP) paradigm [66]. This increase will correlate with clinical outcomes.The high-dose group will show a greater improvement in alcohol-related parameters than the active placebo group (↑ abstinence self-efficacy, ↑ motivation to change, ↓ craving). These improvements will correlate with clinical outcomes.

Exploratory outcomes:

Modulations of EEG-derived measures of alcohol cue reactivity and inhibition will be compared across groups, and their relationship with clinical outcomes will be investigated.We will explore the impact of the quality of the acute psilocybin journey, in terms of experiential avoidance vs. acceptance, mystical experience, and trauma processing, on clinical outcomes.We will explore the impact of the therapeutic alliance on the quality of the psilocybin experience and on clinical outcomes.We will explore the impact of psilocybin on self-reported interoception and its associations with clinical outcomes.

Blinding and expectancy will be assessed systematically.

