#### Sample size

In line with extant studies indicating medium to large effects of PAT on alcohol consumption in patients with AUD (Cohen’s d = 1, [54]; Hedges’ g = 0.52 [15]), the sample size was calculated to observe a medium-size effect (Cohen’s f = 0.25) with a power of 0.9 and a type I error set at 0.05. A priori power calculation based on the primary clinical hypothesis (mixed-design analysis of variance, two groups: high dose vs. active placebo; two timepoints: % heavy drinking days from 8 weeks prehospitalization to 1 day prehospitalization vs. % heavy drinking days from hospital discharge to 4 weeks posthospital discharge) indicated a needed sample size of *n* = 46. Accounting for 25% attrition, we set the total sample size to *n* = 62. If the drop-out rate is higher, we will continue to include participants until 46 have completed visit 14 (primary clinical outcome).

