#### Psychological processes and alcohol-related parameters

The difference between both treatment arms with respect to change from baseline to one week post-psilocybin administration, as well as four weeks, three and six months posthospital discharge on the following scales:

The Acceptance and Action Questionnaire II (AAQII; [110]) to assess the construct of psychological (in)flexibility.The Multidimensional Assessment of Interoceptive Awareness (MAIA; [111]) to evaluate interoceptive processes across 8 dimensions: noticing, trusting, not distracting, not worrying, attention regulation, emotional awareness, self-regulation, and body listening.The Watts Connectedness Scale (WCS; [63]) to measure felt connectedness to self, others, and the world.The Penn Alcohol Craving Scale (PACS; [112]) to assess the frequency, intensity, and duration of past-week cravings.The Alcohol Abstinence Self-Efficacy Scale (AASE; [113]) to evaluate participants’ confidence in their ability to resist drinking alcohol in high-risk situations.Readiness to change alcohol consumption behavior will be measured by collecting Likert-scale ratings of the participants’ (1) perception of the importance of change in drinking; (2) confidence in their ability to change; (3) readiness for change and (4) commitment to the goal of abstinence [15].

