### Data analysis

The data will be analyzed according to a statistical analysis plan that will be uploaded on ClinicalTrials.gov before unmasking. Significance levels for all analyses will be set at 0.05. Clinical outcome analyses (alcohol consumption parameters) will be performed on the intention-to-treat population, including all randomized patients who have completed the dosing session (visit 7). Changes in continuous outcomes will be analyzed with mixed-model analysis of variance with Helmert contrasts when indicated. For time series analysis, general linear mixed models will be used in the case of missing data. Mediation analyses will be used to evaluate whether hypothesized mechanistic variables mediate the effect of treatment on clinical improvements, for example, whether the mystical experience score during psilocybin administration mediates the impact of treatment on changes in the percentage of heavy drinking days. Treatment-emergent adverse events will be classified, tabulated, and treatment groups contrasted using Chi squared or Fisher’s exact test.

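### For secondary outcomes with three or more time points, the only named contrast (Helmert) does not test change from baseline to 6 months

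*Protocol article*

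**What the plan says.** The Data analysis section assigns changes in continuous outcomes to "mixed-model analysis of variance with Helmert contrasts when indicated". It does not give the direction of the coding, the outcomes concerned or what would count as an indication, and it names no other contrast. It defers detail to a statistical analysis plan that is to be posted before unmasking.

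The outcomes are defined as changes to particular visits:

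- The first secondary hypothesis in the Proposed study section includes the percentage "of heavy drinking days at 6 months posthospital discharge", with drinks per day and abstinent days at both 4 weeks and 6 months.
- The Secondary clinical outcomes section defines arm differences in change from baseline to 4 weeks and to 6 months for drinking and symptom measures.
- The Psychological processes section asks for change from baseline to one week after dosing, "as well as four weeks, three and six months posthospital discharge on the following scales".
- The Neurocognitive mechanisms section asks for change from baseline to one day and to one week after dosing.

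The primary outcome differs. The Sample size section sets it up as "mixed-design analysis of variance, two groups: high dose vs. active placebo; two timepoints".

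**The concern.** Helmert coding compares each level with the average of the later levels (forward) or of the earlier levels (reverse). With two levels this is the ordinary change score. With three or more, the contrasts answer questions about averages over visits, and the stated 6-month outcomes are not among them.

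At stake is what gets reported for the 6-month drinking hypotheses and for the other multi-visit secondary outcomes. If a Helmert contrast is presented as the 6-month result, its estimate is not the 6-month change from baseline, and its power can be well below that of the direct comparison. The unstated direction also leaves open which of two contrast sets, answering different questions, will be used.

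**Working it through.** **Inputs from the protocol article.** Sample size section: f = 0.25, "with a power of 0.9 and a type I error set at 0.05", 46 completers, 62 in total. Data analysis section: 0.05 for all analyses. Trial design section: 1:1 allocation, so 23 completers per arm.

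**Assumptions.** The correlation rho between repeated measures is not stated. I take 0.5 and show 0 to 0.7. I also assume compound symmetry, SD = 1 at each visit and 46 completers at every visit.

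**1. The plan's own figure.** For the 2 × 2 group-by-time interaction, lambda = N·m·f²/(1 − rho) with m = 2. At N = 46 and rho = 0.5:

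lambda = 46 × 2 × 0.0625/0.5 = 11.5, on 1 and 44 df, power 0.9125.

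This is the smallest even N that reaches 0.90. For attrition, 46/0.75 = 61.3, rounded up to 62. Both stated figures reproduce. In this design f = D/4, where D is the arm difference in change, so f = 0.25 means D = 1 SD.

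**2. Two levels (primary outcome).** Forward, reverse and simple coding all reduce to (−1, 1). The estimate is D and power is 0.91 under each.

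**3. Three levels (drinking outcomes).** Let b, w and s be the arm differences at baseline, 4 weeks and 6 months.

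- Forward: F1 = (w + s)/2 − b; F2 = s − w.
- Reverse: R1 = w − b; R2 = s − (b + w)/2.
- Simple: S1 = w − b; S2 = s − b.

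S2 is in neither Helmert set. It can be rebuilt from either: S2 = F1 + F2/2 = R2 + R1/2. The fitted model therefore already holds the direct contrast.

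| Profile (b, w, s) | F1, F2 | R1, R2 | S1, S2 |
|---|---|---|---|
| 0, D, D (sustained) | D, 0 | D, 0.5D | D, D |
| 0, D, 0.5D (half faded) | 0.75D, −0.5D | D, 0 | D, 0.5D |
| 0, 0, D (6 months only) | 0.5D, D | 0, D | 0, D |

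**4. Power for a sustained effect, D = 1 SD.** The standard error is √[(1 − rho) × Σc² × 2/23], with a t test on 44 df, two-sided 0.05.

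- S2: Σc² = 2, SE = 0.295, 1/0.295 = 3.39, power 0.91.
- R2: Σc² = 1.5, SE = 0.255, 0.5/0.255 = 1.96, power 0.48.
- F1: Σc² = 1.5, SE = 0.255, 1/0.255 = 3.92, power 0.97.
- F2: true value 0, rejection rate 0.05.

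The same formula over rho:

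| rho | S2 | R2 | F1 |
|---|---|---|---|
| 0 | 0.65 | 0.27 | 0.77 |
| 0.25 | 0.77 | 0.35 | 0.88 |
| 0.5 | 0.91 | 0.48 | 0.97 |
| 0.6 | 0.96 | 0.57 | 0.99 |
| 0.7 | 0.99 | 0.70 | >0.99 |

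For a 6-month-only effect, F1 is 0.5 D with power 0.48 at rho = 0.5.

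**5. More levels.** With baseline, 4 weeks, 3 months and 6 months and a sustained effect, the last reverse contrast is D − (0 + D + D)/3 = 0.33 D, power 0.27. With the five visits that Table 1 shows for the scales (days −20, −1, +7, +35, +190) and an effect from day +7 on, the last reverse contrast is D − (0 + 0 + D + D)/4 = 0.5 D, power 0.56. In that layout the first forward contrast is (0 + D + D + D)/4 = 0.75 D, because day −1 precedes dosing. The second forward contrast, day −1 against the later visits, is the full D. Whether day −1 enters the model is not stated, and the Psychological processes section does not list it among its change points.

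**The case against.** Several counter-arguments have force.

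- **The overall test does not depend on coding.** The group-by-time F test is the same under any full set of contrasts. This is correct, but with three or more levels it does not say at which visit the arms differ, and the 6-month hypothesis is about one visit.
- **Some hypotheses name no visit.** Those on mood, flexibility, neuroplasticity and craving speak only of greater improvement. Baseline against pooled later visits is a defensible test of these, and for the EEG measures a sensible one. This stands for the hypotheses. The outcome sections, however, list named visits, and the drinking hypothesis names 6 months outright.
- **The wording is conditional and the analysis plan is not shown.** It may add direct contrasts. This limits the severity. The point here is not something left unsaid: the article names one contrast type, and the condition can matter only where there are three or more levels.

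A reader might also infer three stronger things that the documents do not support:

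- That the primary test or the sample size is compromised. With two time points the codings are identical.
- That the 4-week drinking change goes untested. The first reverse contrast is exactly that change.
- That a durable effect would vanish. Under forward coding it appears in full in the pooled contrast, with more power than the direct one. The zero for 4 weeks against 6 months is then the right answer, since it shows durability. Halving belongs to reverse coding and the zero to forward coding, so they cannot both describe one analysis.

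**Conclusion.** The point holds in a limited form. For secondary continuous outcomes with three or more time points, the one contrast family named does not match the change-from-baseline outcomes, and neither direction contains 6 months minus baseline.

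The algebra needs no assumptions. The power loss does: 0.48 against 0.91 applies to reverse coding, a sustained 1 SD effect, rho = 0.5, compound symmetry and 23 completers per arm at 6 months. Over rho from 0 to 0.7 the pair runs from 0.27 against 0.65 to 0.70 against 0.99. Under forward coding the problem is one of meaning more than power: a sustained effect is detected, but as an average over follow-up and not at 6 months.

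This is worth correcting before unmasking. It does not threaten the primary result.

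**What to change.** In the Data analysis section, and in the statistical analysis plan before it is posted, replace the Helmert phrase with arm-by-time contrasts from the mixed model, each against the baseline that the outcome sections define:

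- drinking and symptom outcomes: 4 weeks and 6 months, as listed for each outcome;
- process and alcohol-related scales: one week after dosing, and 4 weeks, 3 months and 6 months after discharge;
- EEG outcomes: one day and one week after dosing.

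If the day −1 measurement is to enter the model or serve as the reference for any scale, say so explicitly, because that changes the baseline from which change is measured. If a pooled follow-up effect is also wanted, name it as a separate contrast.

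The cost is about one sentence. No data, visits or participants are added, because the direct contrasts are linear combinations of what the model already estimates. If the analysis plan already uses direct contrasts, it need only note the departure from the published wording.

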## Discussion

Although our study aims to address limitations that have been raised within PAT research while investigating questions that currently remain unanswered, some issues might arise from our design. First, the choice to opt for an active placebo group that receives a low yet psychoactive dose of 5 mg of psilocybin involves some risks. Although we hope to maintain blinding or at least increase group allocation ambivalence and therefore reduce the bias induced by large placebo and nocebo effects in the experimental and control groups, respectively, we might be unsuccessful. It is unclear to what extent the effects of a low dose might be mistaken for those of a high dose, and this might depend on individual factors such as past psychedelic experience and sensitivity to psychedelic effects. Moreover, our approach might decrease the effect sizes pertaining to group differences, as even low doses of psilocybin show considerable occupancy of cortical 5-HT_2A_Rs [116] and may therefore induce a therapeutic effect.

Second, while our trial aims to be pragmatic and include a more representative, diverse pool of participants by recruiting directly from within the hospital, we must adhere to safety guidelines and respect strict and rather restrictive inclusion and exclusion criteria, which limits the range of individuals we can include.

Third, as we propose the experimental treatment integrated within a real-world clinical pathway, participation may influence patients’ relationships with other inpatients not included in the study, which might impact social relations during detoxification, thereby affecting treatment trajectory.

Last, our study includes a single dosing session, which might not be enough. Contemporary clinical studies have involved one to three dosing sessions (e.g., [38, 39, 117]), with two psilocybin sessions proposed in the only RCT of PAT for AUD [15]. Interestingly, important decreases in the number of heavy drinking days were already observed after the first session, suggesting a therapeutically significant effect of a single administration. An ongoing trial compares the clinical efficacy of one versus two dosing sessions on major depressive disorder with co-occurring AUD (NCT04620759), which will inform the development of future interventions.

## Data Availability

No datasets were generated or analysed during the current study.

## Abbreviations

ACT: Acceptance and Commitment Therapy
AUD: Alcohol Use Disorder
CIWA-AR: Clinical Institute Withdrawal Assessment Alcohol Scale Revised
DMT: Dimethyltryptamine
DSM-5-TR: Diagnostic and Statistical Manual of Mental Disorders, Fifth Edition, Text Revision
I-RISA: Impaired Response Inhibition and Salience Attribution
LSD: Lysergic Acid Diethylamide
LTP: Long-Term Potentiation
mGluR2: Metabotropic Glutamate Receptor 2
PAT: Psychedelic-Assisted Therapy
PEth: Phosphatidyl-ethanol
PROM: Patient Reported Outcome Measures
RCT: Randomized Controlled Trial
sAUD: Severe Alcohol Use Disorder
SPIRIT: Standard Protocol Items:Recommendations for Interventional Trials
TLFB: Timeline Follow-Back
5-HT2AR: Serotonin 2A Receptor
5-MeO-DMT: 5-Methoxy-N,N-dimethyltryptamine
